## Method/Design

Design: Cluster randomized trial, controlled and multicentric, comparing one group of patients that take part in the Health Workshops, with another group of similar characteristics that don't.

Setting: The study will be done in Heath Care Centers of Barcelona City.

Randomization unit: Primary care Teams (PCT)

Study Population: Population around the Centers that participate in the Study and that meet the criteria of inclusion.

Inclusion criteria:

• Persons of both sexes between 18 and 65 who consent to do so.

Exclusion criteria:

• If there is an objection to participating during a period of 12 months.

• If there a language difficulty, unable to understand or express in Spanish or Catalan.

• If there are acute mental problems.

• Other health problems which may be a difficulty in following the workshop, (like terminals, organic pathology...).

Sample size calculation: Accepting an Alfa risk of 0.05 and a Beta risk of 0.2 in a bilateral contrast, 108 individuals per group are needed in order to detect how statistically effective it is in a 20% difference between groups in quality of life with the SF-36 Questionnaire. We have estimated a 10% rate of loss in participation. The ARCOSENO approximation has been used.

Variables in the study: We collect socio-demographic variables from all participants: age, sex, studies, employment or work situation.

Principal Variable: HRQOL measured by means of SF-36 Questionnaire. We have selected the quality of life perceived indicator as the main variable as it is sensible to small changes [19].

Variables related to the intervention:

• Number of sessions the person has attended.

• IPAC Questionnaire for variables related to physical activity (the IPAC questionnaire has been used in research around this area so it allows us to compare the data obtained.)

• The variables related to eating habits will be collected by means of Questionnaire PREDIMED [15], which is validated and used in our area, as so allow us to compare results.

• Blood Pressure, Lipid Profile, Height, Weight, will be gathered from the computerized clinical history.

• To estimate the costs we will add the time spent by professionals directly related with the intervention (telephone calls, meetings with participants, gathering of data, workshops...)

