• Gathering of information: the gathering of data will be done in both groups, (intervention and control groups): before each intervention (Health Workshop), at the end of the intervention and in 6 months and 12 through self administered questionnaires in Teleform^© ^format.

Description of the Study (Figure 1)

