### Data analysis

The analysis will be done on an intention to treat basis. Those who have done less than six sessions will be considered withdrawals.

The descriptive analysis will be done in proportion to the quality variables and the average values for the quantities, with the corresponding measures of dispersion.

To observe the effect of the intervention in quality of life related to health, the change of habits and the costs derived from related resources, the T-Tests will be used for paired data and the McNemar Test or equivalents for quantitative or qualitative variables or their non parametric equivalents, if the distribution of the variable does not comply with the criteria of normality (Kolmogorov-Smirnof).

To analyze the factors that have influence over the changes of quality of life related to health (CVRS) and those related with the intervention, models of multiple regressions will be used. In each regression model the dependent variable will be derived from the calculation or the difference between ratings in the beginning of the study and the ratings at the end of the SF-36; the rest of the variables determined in the study will be included as independent variables. As the first step in the analysis of regression the adequate diagnosis will be done to detect extreme values and verify conditions of applicability (homocedastisity, normality and independence of waste). If needed the necessary transformations will be done in the dependent variables for the fulfillment of applicability conditions. The criteria of selection of variables for the estimation of multivariable models will be a Forward-Stepwise with the criteria of input of p < 0.05 and a criteria of output of p > 0.10.

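### No stated SF-36 analysis uses the three follow-up questionnaires jointly, and the regression outcome is a two-point change with an undefined end visit, so the intention-to-treat basis is not secured

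*Protocol article*

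**What the plan says.** All statements are in the protocol article.

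- *Method/Design*, gathering of information: both groups complete questionnaires before the workshop and then "at the end of the intervention and in 6 months and 12". That makes one baseline and three follow-up forms.
- *Data analysis*, analysis set: "The analysis will be done on an intention to treat basis". The next sentence counts anyone with fewer than six sessions as a withdrawal. It does not say whether such people stay in the analysis.
- *Data analysis*, effect of the intervention: paired t-tests, McNemar tests or non-parametric equivalents, with no visit named. The *Abstract* lists Student's t, chi-square and logistic regression, none of which is a repeated-measures method.
- *Data analysis*, regressions on factors influencing change: the dependent variable is the difference between the starting score and "the ratings at the end of the SF-36". The other study variables are candidate independent variables.
- *Method/Design*, sample size: "We have estimated a 10% rate of loss in participation".

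The end is not defined. The description of the control group, under the study phases, places the last evaluation at 12 months, but the close of the eight-week workshop is also a possible reading.

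**The concern.** Both a two-point change and a paired test need two observed scores per person. Someone who returned the baseline, end-of-workshop and 6-month forms but not the 12-month form has no 12-month change. Unless the value is imputed, that person contributes nothing to the comparison, although the article claims intention to treat and expects loss.

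Two things are at stake. The first is bias: if people who see little early gain stop answering, mainly in the workshop arm, those who remain make the workshop look better than it is. The second is wasted information. The *Background* motivates the trial by noting that gains from group education fade after the group ends, and three follow-up forms are collected, yet no stated method reads them together.

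**Working it through.** **1. The plan's own figure.** The inputs are "Accepting an Alfa risk of 0.05 and a Beta risk of 0.2 in a bilateral contrast", "108 individuals per group are needed", a "20% difference between groups in quality of life with the SF-36 Questionnaire" and "The ARCOSENO approximation has been used". The base proportion is not given; I assume 40% against 60%, the pair that needs the largest sample.

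- h = 2·asin(√0.6) − 2·asin(√0.4) = 0.4027
- n = 2·((1.960 + 0.842)/0.4027)² = 96.8, so 97 per arm
- With 10% loss: 97/0.9 = 107.8, so 108 per arm. The stated figure is reproduced.

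**2. How much data is involved.** There are four planned forms and the change score uses two. Two of the three follow-up forms therefore stay out of the regression outcome, whichever visit the end means. At 10% loss, 108 × 0.9 = 97.2 remain, so about 11 per arm have no final score.

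**3. Is it a power problem?** Under 40% against 60%, ignoring clustering:

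| Loss | Remaining per arm | Power |
|---|---|---|
| 10% (planned) | 97.2 | 80.2% |
| 20% (assumed) | 86.4 | 75.4% |
| 30% (assumed) | 75.6 | 69.7% |

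At the planned loss the sample size already covers the loss of precision. Any problem is one of bias.

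**4. Possible bias.** Assumptions, none of them from the article: no true effect; scores with SD 1 and the same correlation r between all visits; the end means 12 months; control loss is random. Workshop-arm loss is logistic in the standardised early change Z (end of workshop minus baseline), with log-odds 1 per SD and the intercept set to give the stated loss.

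- The covariance of the 12-month change with the early change is 1 − r, and the early change has SD √(2(1 − r)). So the expected 12-month change given Z is √((1 − r)/2)·Z.
- Spurious gain = √((1 − r)/2) × mean Z among those retained.
- By numerical integration, mean Z among those retained is 0.0908 at 10% loss and 0.1732 at 20%.

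| r | Spurious gain, 10% loss | Spurious gain, 20% loss |
|---|---|---|
| 0.5 | 0.500 × 0.0908 = 0.045 SD | 0.087 SD |
| 0.6 | 0.447 × 0.0908 = 0.041 SD | 0.077 SD |
| 0.7 | 0.387 × 0.0908 = 0.035 SD | 0.067 SD |

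Halving the assumed dependence to log-odds 0.5 gives 0.019 to 0.024 SD at 10% loss.

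**5. Against the noise.** The standard error of the difference in mean change with 97 per arm is √(2 × 2(1 − r)/97): 0.144 SD at r = 0.5 and 0.111 SD at r = 0.7, ignoring clustering. The ratios are 0.045/0.144 = 0.31 and 0.035/0.111 = 0.32, about a third of a standard error.

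**6. What removes it.** In a simulation of 2,000,000 people per arm under the same assumptions:

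- Adjusting completers for baseline alone leaves 0.023 to 0.026 SD at 10% loss.
- Predicting the missing 12-month score from the baseline and end-of-workshop scores leaves at most 0.0015 SD, which is close to simulation error.

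The second check stands in for a likelihood model of all visits; the mixed model itself was not fitted.

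**The case against.** A reader might infer that the plan discards non-responders and so contradicts its own intention-to-treat claim. The article does not support that. It states how the dependent variable is calculated and gives no rule for people without a final form: neither exclusion nor imputation. Imputation, including from the earlier forms, is compatible with a change score. It may be specified in a full protocol or analysis plan that is not shown, so silence about it is no fault here.

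A reader might also infer that the first-to-last difference is the only SF-36 outcome. That goes too far as well. The sentence belongs to the regressions on influencing factors. The effect is tested in the preceding paragraph, and paired tests could be run at each follow-up. Interim scores might even enter the regressions as independent variables, though not as outcomes.

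If the end means the close of the workshop, the mechanism in step 4 largely disappears, because the outcome is then the early change itself. The bias figures also rest on an assumed, one-arm dropout mechanism and are small. The six-session sentence is a more direct textual tension with intention to treat than the change score.

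All of this stands, and it limits the point. Three things remain: the outcome of the regressions is fixed at two time points, its second time point is not identified, and no described method uses the follow-ups together. Imputation would not bring the interim scores in unless it used them.

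**Conclusion.** The point holds in a narrow form, as a worthwhile improvement rather than a serious defect. The article claims intention to treat, but its stated SF-36 methods secure it only if missing values are handled by some means not described here.

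If nothing is imputed and the end means 12 months, the spurious gain is about 0.04 SD at the planned 10% loss and 0.07 to 0.09 SD at 20%. Those sizes depend on the assumed workshop-arm dropout (log-odds 1 per SD), random control loss and visit correlations of 0.5 to 0.7. With weaker dependence or another end visit they shrink. At the planned loss there is no power shortfall from this source, given the assumed 40% against 60% and no clustering.

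**What to change.** Change the analysis wording as follows.

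- State 12 months as the primary visit.
- Estimate the between-arm contrast at that visit from one mixed model of all post-baseline SF-36 scores (end of workshop, 6 and 12 months). Include arm, visit, arm-by-visit, baseline SF-36 and visit-by-baseline, with an unstructured within-person covariance. Add a random effect for primary care team, to match the cluster design in *Method/Design*.
- Include everyone randomised who has at least one post-baseline form, in the assigned arm, whatever the number of sessions attended. This also settles what the six-session sentence means for the main analysis.
- Keep the change-score regressions as exploratory.

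No new data are needed. The cost is a somewhat more complex model that is valid if loss depends on observed scores. It still omits people with no post-baseline form, so their number should be reported by arm.

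### The stepwise regression of SF-36 change may drop or partly adjust away study arm, so it should not serve as the adjusted between-arm estimate

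*Protocol article*

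**What the plan says.** The Data analysis section sets two tasks. The effect of the intervention on quality of life, habits and costs goes to t-tests for paired data, McNemar tests or non-parametric equivalents. The factors associated with SF-36 change, and those tied to the intervention, go to multiple regression.

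For that regression:

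- The dependent variable is the difference between the first and last SF-36 ratings.
- On covariates, "the rest of the variables determined in the study will be included as independent variables".
- The criterion of variable selection "for the estimation of multivariable models will be a Forward-Stepwise" rule, with entry at p < 0.05 and removal at p > 0.10.
- Study arm is not mentioned, and no time point is given for any covariate.

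Method/Design lists among the study variables "Number of sessions the person has attended", the physical activity questionnaire, the diet questionnaire, blood pressure, lipids, height and weight. Questionnaires are collected before the workshop, at its end, and at 6 and 12 months. A lipid profile is repeated after 12 months. The workshop is delivered only to the intervention group, and controls may be offered it once the 12-month evaluation is over. The Objectives section names better diet, regular activity and controlled risk factors as things the workshop should achieve.

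The Abstract describes the analysis differently: Student's t and chi-square tests of differences, plus a logistic regression.

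**The concern.** Three features of the stated rule work against a valid arm coefficient.

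1. **Sessions attended duplicates arm.** It is zero for every control and positive for nearly everyone in the intervention group. It arises after randomisation and has no baseline value. With both variables on offer, the rule may take either one, and if both enter, the arm coefficient becomes very imprecise.
2. **Diet and activity are intended effects.** If their follow-up values enter, the arm coefficient no longer includes any SF-36 benefit that runs through better habits.
3. **Arm has to win selection.** It is reported only in samples where it passes the p-value threshold. Its coefficient is then biased upward when nothing else is distorting it, and the usual p-value and interval take no account of the selection.

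The principal objective is effectiveness on the SF-36. As specified, the effect tests in Data analysis are paired, that is, within person. The regression is therefore the only analysis in that section that could carry an adjusted contrast between arms. If it is used that way, the result would not be the effect of being offered the workshop.

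**Working it through.** **Planned size, to set the scale.** Inputs from Method/Design: "Accepting an Alfa risk of 0.05 and a Beta risk of 0.2 in a bilateral contrast"; "a 20% difference between groups in quality of life with the SF-36 Questionnaire"; "108 individuals per group are needed"; "We have estimated a 10% rate of loss in participation"; "The ARCOSENO approximation has been used". The base proportion is not given. I assume 0.40 versus 0.60, the least favourable pair for a 20-point difference.

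- h = 2·asin(√0.60) − 2·asin(√0.40) ≈ 0.40
- n = 2·((1.960 + 0.842)/h)² = 96.79, so 97 per group
- 97/(1 − 0.10) = 107.8, so 108 per group

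The planned 108 reproduces. The illustrations below use 97 per arm and an effect of 0.4 SD, which matches h.

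**Collinearity of sessions with arm.** Assume a 1:1 split, zero sessions in controls, and 8 sessions each attended with probability 0.8 in the intervention arm (mean 6.4, variance 8 × 0.8 × 0.2 = 1.28).

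- r² = 0.25 × 6.4² / (0.25 × 6.4² + 0.5 × 1.28) = 10.24/10.88 = 0.941, so r = 0.97
- Variance inflation = 1/(1 − 0.941) ≈ 17, so the SE of arm is about 4 times larger with both in the model

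With more variable attendance (mean about 6.1 sessions, 27% attending fewer than six), r = 0.90. The inflation is then 1/(1 − 0.81) = 5.3, an SE ratio of about 2.3. In the simulation with that attendance, entering all variables raised the SE of arm from 0.14 to 0.33–0.34.

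**Adjustment for intended effects.** If a share s of a 0.4 SD effect runs through diet and activity, the arm coefficient adjusted for them is 0.4 × (1 − s): 0.40, 0.20 and 0.00 for s = 0, 0.5 and 1. Simulation returned the same values.

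**The stated selection rule.** There were 1,000 simulated trials per scenario, with entry at 0.05 and removal at 0.10. Candidates were arm, sessions, two follow-up habit measures (each shifted 0.5 SD by the workshop) and covariates with no effect (six in set A, eight in set B). Set A uses the more variable attendance, set B the 80% attendance.

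| Set | Share mediated | Arm alone significant | Arm retained by the rule |
|---|---|---|---|
| A | none | 77% | 59% |
| A | half | 82% | 26% |
| B | none | 80% | 51% |
| B | half | 78% | 22% |
| B | all | 79% | 3% |

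In set A without mediation, the arm coefficient averaged 0.49 in the trials that kept it, against a true 0.40 (0.49/0.40 = 1.22, about 22% too large). In set B with half mediation, offering only arm and the eight no-effect covariates kept arm in 82% of trials.

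The documents give neither attendance, nor the shift in habits, nor the share mediated. All three are assumptions.

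**The case against.** The strongest reply is that this model is not the effect estimator. Data analysis gives the effect to separate tests and gives the regression the job of finding influencing factors, where sessions, diet and activity are natural candidates. The Abstract adds Student's t and chi-square tests, naturally read as comparisons between groups with no selection. This stands. A reader might infer that the plan deletes the trial's treatment effect, and the documents do not support that: dropping arm here cannot remove a result reported from another test.

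A second reply is that post-intervention covariates are inferred. This also stands in part. The article gives no time point, and follow-up blood pressure and weight are only implied by the objectives. The wording permits follow-up values without specifying them. The argument about sessions attended does not depend on this, since that variable exists only after randomisation.

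A third reply is that silence on forcing arm in may be a detail left to a fuller document. That is fair as far as it goes. The point rests on what the article does fix, namely an unrestricted candidate list and a p-value rule.

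Finally, arm dropped does not always mean effect lost. In set B without mediation, sessions was retained in 32% of trials, so some of the workshop signal survives as exposure. But a sessions coefficient describes attendance, not assignment, and so does not give the intention-to-treat contrast that Data analysis promises.

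**Conclusion.** The concern holds in a limited form. As written, the regression cannot be relied on to yield an adjusted between-arm effect on SF-36 change: arm may be dropped, may share its effect with sessions attended, or may lose the part that runs through follow-up diet and activity, and its p-value and interval ignore the selection. This matters if the regression is used as the adjusted effectiveness estimate, a role that no other analysis in the Data analysis section can fill. It does not invalidate the separate tests.

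Under the assumed inputs, the rule kept arm in about 3% to 59% of trials, against about 80% (77% to 82%) significant with arm alone. Every scenario pointed the same way, but the size depends on attendance, habit shift and mediation share, so the range is not a forecast for this trial. It should be fixed, as a weakness in a secondary analysis that could be taken for the main one.

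**What to change.** Prespecify one effectiveness model for the SF-36: arm forced in; baseline SF-36 and a short list of the socio-demographic variables already collected (age, sex, studies, employment) as covariates; no stepwise selection.

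Label the stepwise regression exploratory and state that it will not support the effectiveness conclusion. Confine sessions attended (within the intervention arm) and post-baseline diet, activity and risk factors to that exploratory work or to a mediation analysis.

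This is a change of wording that uses data already planned. The cost is slightly more analysis. How the model should reflect randomisation by primary care team is a separate question.

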### Quality control

The proceedings used to guaranty the quality of the information are the following:

• The intervention is done by the persons in the research group who created all the educational material being used in the session, which guarantees a homogenous intervention.

• The gathering of data is done through self-operated questionnaires in Teleform^©^. This automated software that reads scanned questionnaires, performs a validating process of the data with previously established parameters, and once the data is validated these are poured into a specifically created database.

• The introduction of information or data will be performed by a person hired to provide technical assistance for this study.

### Ethical aspects

It will be an indispensable requisite to participate in this study that all participants sign their informed consent. The same document specifies that the participation has to be voluntary, with the possibility of leaving the program if he or she so desires, and that the intervention will not have a negative effect in their health care assistance. They will be given both oral and written information. The subjects will have opportunities to ask questions about any detail of the study.

The protocol has been evaluated by the Ethical Committee in Clinical Investigation (CEIC) of the Research Institute of Primary Attention (IDAP) Jordi Gol and counts with its approval.

Confidentiality of the information: only the researchers will have access to the data of the subjects who accept. Once the study is finished, both the control group and the group intervened will be informed of the results; once the effectiveness of the Health Workshop is proven, they will be invited to participate.

## Discussion

The Health Workshop proposed in the present study is a different approach to Health Promotion, placing the emphasis on self responsibly of the persons being cared for.

The weekly cadence of a session during 8 weeks with recommendations of activities and exercises for the week as well as group support is an opportunity to incorporate healthy habits and make a commitment to self-care.

The hand outs as a reminder and reference provide a Health Manual to consult once the Workshop is over.
